## Abstract

**Background:**

Caring for people with dementia (PWD) is stressful and poses many life challenges for the family caregivers. Interventions targeting the stress and psychological well-being of the caregivers have been proposed but the sustainable effects and efficacies of these interventions vary considerably. Mindfulness-based cognitive therapy (MBCT) has been shown to be effective at reducing stress in several populations. However, limited research on the effects of MBCT in family caregivers of PWD has been conducted. This study protocol aims to examine the effects on stress reduction of a modified MBCT for family caregivers of PWD.

**Methods:**

A prospective, single-blind, parallel-group, randomized controlled trial will be adopted. A convenience sample of 100 community-dwelling family caregivers of PWD will be randomized to either the modified MBCT or the control groups. The modified MBCT group will receive a 10-week, seven-session, group-based modified MBCT whereas the control group will receive a social interaction and routine education (SIRE) on dementia care program at a frequency and timing similar to those in the intervention group. The primary outcomes (stress) and secondary outcomes (depression, anxiety, burden, health-related quality of life, and the behavioral and psychological symptoms of the care recipient) will be measured immediately post-intervention (T1) and at 6-month follow-up (T2), which will be compared with the baseline (T0).

**Discussion:**

Reducing the stress of caregiving can promote the well-being of the family caregivers and maintain their sustainability in providing daily care for their family members with dementia. MBCT is found to be effective for stress reduction in other populations, and the results of this study are able to provide us with evidence for using MBCT as a standard supportive intervention for the family caregivers of PWD.

**Trial registration:**

ClinicalTrials.gov, NCT03354819. Registered on 28 November 2017.

**Electronic supplementary material:**

The online version of this article (10.1186/s13063-019-3432-2) contains supplementary material, which is available to authorized users.

## Background

Dementia is a common neurodegenerative disease in older people causing gradual cognitive decline and a series of behavioral and psychological symptoms of dementia (BPSD). As the disease progresses, the self-care ability of people with dementia (PWD) will gradually be lost. Family caregivers play an important role in caring for PWD, and this challenging role usually results in chronic stress and negative emotions [1]. Nowadays, there are different types of nonpharmacological interventions designed for the caregivers. However, the existing evidence supporting the current interventions in stress reduction for family caregivers of PWD is still weak with a small effect size (Cohen’s *d* = 0.18–0.27) [2]. Some studies found that support groups and respite care cannot significantly reduce the stress level of caregivers, although they can provide caregivers with skills, knowledge, and transient support on caring for PWD [3, 4].

Stress is a two-way process that involves the presence of the stressors in the environment and the response and appraisal of an individual subjected to those stressors [5]. Most of the current interventions such as respite care adopt a problem-solving approach and aim to manipulate the stressors of the family caregiver of PWD. However, caregiving stress is chronic and most of it is related to the cognitive decline of the care recipients which is difficult to modify. Thus, an emotion-focused approach is usually adopted for managing stress in the caregivers of PWD [6].

In the past few decades, mindfulness-based intervention (MBI) has been found to be effective at improving a few of the main psychological symptoms, including anxiety, depression, psychotic symptoms, and stress [7–12]. The most commonly used MBI is the Mindfulness-Based Stress Reduction (MBSR) program [13] and mindfulness-based cognitive therapy (MBCT) [14]. The MBSR was developed by Jon Kabat-Zinn in 1970 at the Stress Reduction Clinic at the University of Massachusetts Medical School and was primarily designed for patients with chronic pain. It is a group-based and multi-component intervention involving a wide range of activities, including sitting meditation, mindful walking, mindful eating, body scanning, group sharing, home practice, and psychoeducation on stress and psychological health. Based on the MBSR, Segal et al. [14] developed the MBCT to prevent a lapse into depression in people with a major depressive disorder. Similar to the MBSR, the program consists of eight 2-h weekly sessions with a 1-day retreat. MBCT adopted the principles of MBSR and integrated cognitive-behavioral techniques that explore more on negative thinking and its impacts on the well-being of participants [14]. Compared with MBSR, MBCT involves imagining particular scenarios and asks the participants to notice what thoughts appear. At the same time, the participants are taught to focus less on reacting to incoming stimuli (stressors) and instead on accepting and observing the stimuli without judgment.

A systematic review was conducted by us which included five experimental studies to investigate the effect of MBI (including MBCT and MBSR) on stress reduction in the family caregivers of PWD [15]. The result showed that the stress levels dropped significantly after an 8-week MBI in the family caregivers of PWD with a moderate aggregated effect size of 0.57 (95% confidence interval (CI) 0.23–0.92, overall effect *Z* = 3.25; *p* = 0.001). While an immediate effect of MBI was seen, the long-term effect (i.e., 6 months after the intervention) was unclear. Furthermore, a limited number of clinical trials and several limitations (such as poor study design, small sample size, lack of information on the adherence rate when practicing mindfulness, and a high attrition rate) were also identified in this review. This signifies that more studies are still required to examine the effects of MBI for family caregivers of PWD.

MBI is a relatively new intervention for stress management in the caregivers of PWD. Therefore, a feasibility study including 53 family caregivers of PWD was conducted between 2016 and 2017 by us to investigate the feasibility of using MBI in family caregivers of PWD, and also to determine which therapeutic modality in mindfulness (MBSR or MBCT) is more effective in reducing stress in the caregivers [16]. The results showed that the family caregivers could master the mindfulness skill after the mindfulness sessions with a low attrition rate of 3.8%. Significant improvement was found for all psychological outcomes, including stress, depression, and burden, in both MBI groups. Compared with MBSR, the MBCT participants had significantly greater improvements in perceived stress (mean difference = 1.74, standard error = 0.78). Based on the suggestions from the focus group interview in the feasibility study, the MBCT protocol was further modified for this main study.

## Methods

### Study design

This is a prospective, single-blind, parallel-group, randomized controlled trial (see Fig. 1 for the Consolidated Standards of Reporting Trials (CONSORT) flow diagram, Fig. 2 for the Standard Protocol Items: Recommendations for Interventional Trials (SPIRIT) figure, and Additional file 1 for the SPIRIT checklist).

**Fig. 1 Fig1:**
[figure not shown]
Consolidated Standards of Reporting Trials (CONSORT) flow diagram. BPSD Behavioral and psychological symptoms of dementia, BRS Brief Resilience Scale, CESDS Center for Epidemiologic Studies Depression Scale, FFMQ Five Facet Mindfulness Questionnaire, HADS-A Hospital Anxiety and Depression Scale-Anxiety, MBCT mindfulness-based cognitive therapy, NGO nongovernmental organization, NPI-Q Neuropsychiatric Inventory Questionnaire, PSS Perceived Stress Scale, PWD people with dementia, SF-12v2 Short-form 12-item health survey version 2, SIRE Social interaction and routine education, ZBI Zarit Burden Scale

**Fig. 2 Fig2:**
[figure not shown]
Standard Protocol Items: Recommendations for Interventional Trials (SPIRIT) figure. BRS Brief Resilience Scale, CESDS Center for Epidemiologic Studies Depression Scale, HADS-A Hospital Anxiety and Depression Scale-Anxiety, MBCT mindfulness-based cognitive therapy, NPI-Q Neuropsychiatric Inventory Questionnaire, PSS Perceived Stress Scale, PWD people with dementia, SF-12v2 Short-form 12-item health survey version 2, SIRE Social interaction and routine education, ZBI Zarit Burden Scale

### Objective

This study aims to investigate the effects of a modified MBCT on stress reduction in the family caregivers of PWD.

### Hypotheses of the study

Participants in the intervention group will have better improvement than the control group after the seven-session, 10-week modified MBCT intervention immediately after the intervention (T1) and/or at 6-month follow-up (T2) in terms of the following hypotheses: 1) significantly greater reduction of stress (primary outcome); and 2) significantly greater improvement in the secondary outcomes, namely depression, anxiety, resilience, burden, health-related quality of life, and the behavioral and psychological symptoms of the care recipient.

In addition, there are two hypotheses to facilitate the explanation of the positive changes in the modified MBCT group: 1) there will be significant positive correlations between the levels of mindfulness of the caregivers (total score of five facets of mindfulness) and the improvement in their stress, depression, anxiety, burden, resilience, health-related quality of life, and/or behavioral and psychological symptoms of the care recipient; and 2) increased use of all facets or individual facets of mindfulness skills of family caregivers will be significantly and positively correlated with the improvements in their psychological outcomes (stress, depression, anxiety, burden, resilience, and/or health-related quality of life).

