### Sample size

The sample size estimation was based on the primary outcome (stress). In the previous systematic review, the effect size of the MBCT for stress reduction was found to have Cohen’s *d* of 0.57 immediately after the intervention [15]. However, the intervention protocol is further modified and its duration is shortened in this proposed study. A conservative effect size Cohen’s *d* of 0.4 was adopted to detect the mean difference in stress reduction between the intervention and control groups. Based on the power analysis using the software G***Power 3.1 on repeated-measures analysis of variance (ANOVA), a sample size of 84 participants will be needed to achieve 80% power at a two-sided 5% significance level. According to the results of the feasibility study in Hong Kong, an attrition rate of 4% was found [16]. By adopting a more conservative estimation of the attrition rate of about 10%, the estimated sample size is at least 100 for this proposed study, 50 per group.

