### Data analysis plan

IBM SPSS 23.0 software will be used for the data analysis. The Kolmogorov–Simonov test will be used for checking normality. To ensure the similarity of the subjects in the two groups (modified MBCT and SIRE) at baseline, the demographics, adherence rate, frequency of mindfulness practice, and the outcome measurements will be compared by using a *t* test for continuous variables and a Chi-square test for categorical variables. Covariates will be controlled in the main analyses if a significant difference of variables is found at baseline. Both per-protocol (PP) and intention-to-treat (ITT) analyses will be performed. In the PP population, we will include the subjects who attend > 70% of the intervention sessions. A sensitivity test will be performed to compare the differences between the ITT and PP results. The aim of conducting both ITT and PP analyses is to uncover factors affecting the use and effectiveness of the modified MBCT, such as noncompliance and acceptability [48].

Descriptive statistic will be used to analyze the recruitment rate, attrition rate, duration, patterns, and consistency of the participants practicing mindfulness to indicate the acceptability of the MBCT. Mixed multivariate modeling (MANOVA) tests will be adopted to investigate the between-group effect (groups: modified MBCT and SIRE), the within-group effect (times: T0, T1, and T2), and the interaction time effect of group by time effect (group × time) on all of the outcome variables including PSS, HADS-A, CESD, ZBI, BRS, NPI-Q, and SF-12v2, and the process indicator (FFMQ). Correlation checking by Pearson’s product moment correlation of all the psychological outcomes including PSS, HADS-A, CESD, ZBI, BRS, NPI-Q, SF-12v2, and the process indicator (FFMQ) at baseline will be performed. If the correlation is too strong (Pearson’s *r* > 0.6), which may result in multicollinearity and violation of the assumption of mixed repeated MANOVA, then two-way repeated ANOVA and Bonferroni’s adjustments will be adopted to prevent a type I error [49]. Post-hoc pairwise comparisons using Tukey’s Honestly Significant Difference (HSD) will be performed to examine the significant difference in the outcomes.

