## Conclusion

According to the recent systematic review, only a few clinical trials have reported a preliminary and short effect of mindfulness in the family caregivers of PWD. To meet the needs for the family caregivers of PWD, this proposed study has collected feedback from family caregivers of PWD and addressed the limitations (i.e., a low adherence rate) from previous studies by modifying the original MBCT protocol. The modified MBCT protocol aims to facilitate and support the family caregivers by cultivating a mindful attitude, empowering themselves to manage their stress, and promoting their resilience. The stress of family caregivers can last a long time, and hence examining the sustainable effects of the modified MBCT (i.e., a 6-month follow-up) is important. This study will also collect other important information on the intervention, including the participants’ adherence to mindfulness practices, level of mindfulness, and qualitative data for better understanding the active ingredients of the modified MBCT. The findings from this proposed randomized controlled trial could provide scientific evidence for the effectiveness of the modified MBCT for family caregivers of PWD. If significant benefits are found, the modified MBCT can be used as a standard supportive intervention for the family caregivers of PWD.

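### Adjustment across the six secondary outcomes depends on baseline correlations above 0.6, so on the default MANOVA route their false-positive rate is not held at 5% once stress improves

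*Protocol article*

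**What the plan says.** In the protocol article, *Hypotheses of the study* makes stress the primary outcome. Its second hypothesis is "significantly greater improvement in the secondary outcomes, namely depression, anxiety, resilience, burden, health-related quality of life", together with the behavioral and psychological symptoms of the care recipient: six secondary outcomes in all. Either hypothesis may be met at either visit: "immediately after the intervention (T1) and/or at 6-month follow-up (T2").

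*Data analysis plan* makes a mixed repeated-measures MANOVA the default. It covers the PSS and all six secondaries together and tests group, time and group × time. Baseline Pearson correlations are inspected, and if they exceed 0.6, "then two-way repeated ANOVA and Bonferroni’s adjustments will be adopted to prevent a type I error". Tukey's HSD is named for post-hoc pairwise comparisons. No adjustment across outcomes is stated for the MANOVA route, and the number of tests that Bonferroni would cover is not given.

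The *Conclusion* adds: "If significant benefits are found, the modified MBCT can be used as a standard supportive intervention", without saying which outcomes count.

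**The concern.** High correlation may be a reason to leave a MANOVA. It is not a reason to decide whether six outcomes need an adjustment. Unadjusted error across several tests is largest when the outcomes are weakly correlated, which is where the plan does not adjust, and smaller when they are strongly correlated, which is where it does.

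The joint MANOVA does not close the gap. It guards the secondaries only when nothing differs between the arms. Because the PSS is in the same test, a true stress benefit can produce a significant result by itself, and the remaining outcomes are then examined without adjustment across them. A statement that the program improves depression, anxiety, burden, resilience, quality of life or the care recipient's symptoms could then rest on chance. This arises in the situation the trial hopes for, a real effect on stress.

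This is a stated rule with an unsuitable trigger, not a detail that the article merely leaves to a fuller document.

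**Working it through.** **The plan's own figure.** No family-wise error rate is given for the secondaries. The only related figure is for stress: "a sample size of 84 participants will be needed to achieve 80% power at a two-sided 5% significance level", with d = 0.4, so f = 0.4/2 = 0.2 for two equal groups. With λ = f²·N·m/(1 − ρ), m = 3 visits and ρ = 0, the interaction test needs N = 82 (λ = 0.04 × 82 × 3 = 9.84), close to 84. It falls to 58 at ρ = 0.3 and 42 at ρ = 0.5, so 84 implies a between-visit correlation near 0 for that test. This does not bear on the present point.

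**Inputs from the article**
- Six secondaries and two visits: 6 × 2 = 12 possible visit-level contrasts.
- Two-sided 5%, the only level stated.
- Stress effect: planned d = 0.4, and 0.57 from the cited systematic review (*Sample size*). The value 0.8 is added as a larger case.
- 50 per group and about 10% attrition: 50 × 0.9 = 45 per arm.

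**Assumptions, not in the article**
- Between-visit correlation 0.5 and between-outcome correlation r from 0 to 0.6.
- No true effect on any secondary; the stress effect is present at T1 and T2.
- The mindfulness questionnaire is left out of the between-group test, because it is measured in the intervention group only.

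**Step 1. Independent tests, no gate.** 1 − 0.95⁶ = 26.5%; 1 − 0.95¹² = 46.0%. These are reference values only, since the plan puts a joint test first.

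**Step 2. MANOVA first, then unadjusted tests (simulation).** The group × time MANOVA is Hotelling's T² on the p = 14 change scores (7 outcomes × T1 and T2): F = T²(2n − p − 1)/[p(2n − 2)]. A false secondary claim means that this is significant and at least one null secondary is then significant at 5%. Follow-up is counted in two ways: one group × time test per outcome (six tests), or 12 visit-level contrasts. The first allows for Tukey's HSD removing the T1/T2 multiplicity within an outcome; the second makes no such allowance.

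| True stress effect | Six group × time tests | 12 visit contrasts |
|---|---|---|
| none | about 4% | about 4% |
| d = 0.4 | 11–13% | 14–17% |
| d = 0.57 | 18–19% | 24–29% |
| d = 0.8 | 19–25% | 32–38% |

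A separate run with 42 per arm (84/2) gave 11% and 14–17%, 16–17% and 23–27%, and 19–24% and 31–39% for the three non-zero effects. Varying the between-visit correlation from 0.3 to 0.7 moved the 12-contrast figure at d = 0.4, r = 0.5 from 17% to between 13% and 25%.

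**Step 3. Apply the plan's own trigger.** Assume that any of the 7 × 6/2 = 21 outcome pairs above 0.6 switches the route, and that Bonferroni then covers 12 tests.
- True r about 0.3 to 0.4: the trial mostly stays on the MANOVA route, and step 2 describes it (about 15% at d = 0.4 over 12 contrasts).
- True r = 0.5: about 65% of trials switch by chance. Overall rates over 12 contrasts are about 8%, 13% and 15% at d = 0.4, 0.57 and 0.8. With the six-test count included, the range starts at about 7%.
- True r = 0.6: about 98% switch, and the rate is about 4%.

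**Step 4. With adjustment on either route.** Over six tests, 0.05/6 = 0.0083 each, and 1 − (1 − 0.0083)⁶ = 4.9% if independent. Over 12, 0.05/12 = 0.0042 each, also 4.9% if independent; the simulated rate was 3.6–5.5%.

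**The case against.** The strongest reply is that the rule is coherent: an omnibus test stands first, and when it is given up for separate ANOVAs, Bonferroni takes its place. That holds when nothing works, where the joint test keeps the rate at about 4%. It fails once the PSS alone can make the joint test significant.

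Second, the trigger may well be met, and the plan would then adjust. This stands, and it limits the size. Unadjusted rates at correlations of 0.6 or above should not be held against the plan, because it adjusts there. But the article gives no between-outcome correlations, so protection depends on a baseline sample statistic that cannot be foreseen.

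Third, Tukey's HSD is planned. It concerns pairwise comparisons within an outcome and may limit the T1/T2 multiplicity, which is why the six-test column is shown. It does not adjust for the number of outcomes.

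Fourth, the outcomes are labeled secondary, and the objective and sample size rest on stress alone. A reader might infer that the plan makes them confirmatory; the article never uses that word. It does pose them as hypotheses of significant improvement. Likewise, the sentence on standard use is a closing remark and not a decision rule, although its wording is not limited to stress.

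**Conclusion.** The concern holds in a limited form. On the MANOVA route, error across the six secondaries is not controlled once stress improves. The chance of at least one false secondary claim is about 11–17% at d = 0.4, 18–29% at d = 0.57 and 19–38% at d = 0.8, against a nominal 5%. The lower ends are for one group × time test per outcome and the upper ends for 12 visit contrasts. All rest on assumed correlations and on no true secondary effects. They describe the trial if between-outcome correlations are about 0.4 or lower. Near 0.5 the overall rate is about 7–15%, and at 0.6 or higher about 4%.

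A reader might infer that a false secondary claim is likely, or that the error is several times 5% whenever the stress effect is real. Neither follows: the joint rates in the table stay below one half, and the plan's own trigger brings them close to 5% when outcomes are strongly correlated. The primary stress result is not affected.

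**What to change.** In *Data analysis plan*, let the 0.6 correlation rule decide only between the MANOVA and separate repeated-measures ANOVAs. State separately that Holm's or Bonferroni's method is applied across the six secondary group × time tests at two-sided 5% on either route, whatever the correlations, and name those six tests as the family. Restricting each secondary to one visit is optional; it would leave the other visit descriptive, although the article calls the sustained effect important.

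Alternatively, label hypothesis 2 exploratory, report estimates with 95% confidence intervals, and limit the *Conclusion* sentence on significant benefits to stress.

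Both options change wording only and need no further data or participants. The first costs some power for individual secondaries (under Bonferroni, 0.0083 per test in place of 0.05). The second gives up confirmatory claims on secondary outcomes.

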### Study setting

The subjects will be recruited from three nongovernmental organizations (with collaborations before) in Hong Kong providing caring services such as respite care and cognitive training for PWD and their caregivers. The centers are located in the three largest districts in Hong Kong, namely Kowloon, Hong Kong Island, and the New Territories, serving more than 10,000 older people and their caregivers.

